## Methods and design

### Study design and setting

A multicentre, single-blind parallel RCT, with randomisation at the participant level and stratification by recruitment site. This trial adopts the SPIRIT guidelines for clinical protocols [32], and Fig. 1 outlines the study schema.

**Fig. 1 Fig1:**
[figure not shown]
Finding My Way-Advanced Study schema

All RCT participation will occur via two web programs. Research survey data will be collected on Qualtrics (hosted by Flinders University) and the FMW-A web program will be hosted on ManageWP with oversight by Flinders University staff.

### Inclusion criteria

Women (1) with a diagnosis of MBC, (2) aged 18 years or older, with (3) estimated life expectancy longer than 6 months (as per treating clinician’s estimate) and (4) sufficient English for informed consent and program comprehension, will be eligible.

### Exclusion criteria

No internet access or active email address, or previous medical history of dementia or cognitive impairment. Women currently receiving face-to-face psychological services are still eligible to participate (i.e., are not excluded). Women currently enrolled in other active psychosocial intervention trials will be excluded to avoid contamination effects, while those enrolled in observational studies will remain eligible.

### Ethics approval and consent to participate

This study has received ethical approval from the Southern Adelaide Clinical Human Research Ethics Committee (SAC-HREC 2021/HRE00407). Study participants provide online written consent via selecting check-box options for each component of participation, followed by confirming overall consent by clicking the ‘Submit Consent’ button.

### Recruitment

Eligible participants will be recruited via two methods.

**Direct approach**: Women will be screened for eligibility by cancer clinicians then approached by research assistants (RAs) at the 10 participating health sites (Flinders Medical Centre, South Australia; Royal Brisbane & Women’s Hospital, Queensland; Canberra Hospital, Australian Capital Territory (ACT); National Capital Private Hospital, ACT; Peter MacCallum Cancer Centre, Victoria; Lake Macquarie Private Hospital, New South Wales (NSW); Maitland Private Hospital, NSW; Mater North Sydney Hospital, NSW; Chris O’Brien Lifehouse, NSW; Campbelltown Hospital, NSW). CIs and AIs are affiliated with each of these recruitment sites and research assistants will be employed in each state to facilitate and oversee recruitment at each recruiting hospital. Women who are screened as ineligible will receive standard care as usual.

**Self-selection:** In response to advertisements and promotion through *professional networks* (e.g., McGrath Foundation; BCNA; Cancer Council SA), *breast cancer advocacy groups / agencies* (e.g., Cancer Voices Australia), and *research databases* (e.g., Register4, BCNA Review & Survey group). Participants who self-refer to the study will self-confirm their eligibility as part of the online consent process.

### Interventions / groups

#### Intervention: Finding My Way-Advanced

FMW-A is a 6-module psychosocial program that addresses commonly experienced concerns raised by women with MBC (see Table 1). Module content is provided in a multimedia format, with video and written personal accounts from women living with MBC, educational videos from health care professionals, self-management activities, downloadable relaxation-mindfulness audio files, print psychoeducation with audio-conversion options, with illustrations and imagery throughout. Two key strategies facilitate usage. First, personalisation and free-choice access: Based on pilot feedback and adult learning literature [31], after viewing an introductory ‘how to use’ tutorial video, all modules will be immediately accessible. Second, engagement/interactivity through the provision of (i) worksheets, activities, and quizzes with immediate feedback; (ii) a ‘favourites’ and ‘notes’ feature to encourage participants to highlight and reflect on relevant content, a ‘where you left off’ feature to enable participants to immediately return to their last accessed page, and (iii) automated weekly email reminders, provided for the first 6-weeks after enrolling. A booster module is provided 10-weeks after enrolment, providing psychoeducation regarding maintaining wellbeing, a summary/review of the program, and links back to key resources. Materials provided to control participants (outlined below) are integrated within a *Resources* section of the intervention, which also provides links to, and information about, other cancer organisations and websites.

**Table 1 Tab1:** Finding My Way-Advanced Intervention content

Module	Content and Features
1: Navigating Healthcare	• Covers issues women face when navigating their healthcare, including who is in their treatment team, communication, and making treatment decisions • Activities: Assertive Communication; Decision Making
2: The Unique Challenges	• Covers coping with fear of progression, living with uncertainty, and living well • Activities: Values clarification; Goal setting; Mindfulness; Worry postponement; Therapeutic Writing; Distress Tolerance
3: Physical Symptoms	• Covers common cancer-related and treatment side effects that women may experience, and how they can cope with these • Activities: Fatigue and Pain Activity Pacing; Relaxation
4: Emotional Distress	• Covers common emotional reactions, including anxiety, depression, stress, and anger, and ways to cope with these emotions. • Activities: Behaviour Activation; Cognitive Restructuring; Mindfulness; Therapeutic Writing
5: How You See Yourself	• Covers changes to body image, intimacy, and identity • Activities: Reducing body dissatisfaction; Acceptance; Exploring Intimacy; Core Attributes Exploration
6: Your Family and Friends	• Covers common concerns women have for their family and friends, and coping with social changes that may occur • Activities: Needs exploration; Assertive Communication; Social Support Exploration

#### Control: Breast Cancer Network Australia’s *My Journey* online

Consistent with other web-intervention trials in cancer [24], the control arm will receive a minimal intervention attention-control online. This will comprise a FMW-A control homepage with two picture-tile links to (i) BCNA’s “*My Journey*” online and app resource, and (ii) *Resources* that provide links to information from other cancer organisations and websites. *My Journey* covers all stages of breast cancer, but is tailored to the cancer stage at sign up, such that control participants will receive MBC-relevant content only. *My Journey* for MBC incorporates and extends the gold-standard “Hope & Hurdles” resources previously made available to women upon diagnosis with MBC in Australia. It provides comprehensive information about diagnosis, information specific to metastatic sites, hormone and HER-2 positive MBC, treatments, support options, practical issues, planning ahead, information for loved ones, podcasts, and personal video stories of women with MBC. If FMW-A efficacy is demonstrated, control participants will be given first access to the program as part of the planned post-trial public dissemination.

### Study procedures and timeline

Figure 2 outlines the flow of participants through the study. Women eligible for the RCT will be directed to the web-program to register, consent and complete T0 baseline measures for the study, following procedures successfully utilised in our previous studies [27]. Randomisation will then occur with participants immediately redirected to their respective homepages. Following baseline assessment, randomisation will occur via an automated computer-program, with participants allocated to either the Intervention condition, or Minimal Intervention Attention-Control condition. Six weeks after enrolment, participants will receive email notification to complete the T1 post-intervention assessment, with T2 and T3 follow-up questionnaire email notifications sent 3 and 6 months later. Non-responders will receive two automated email reminders, and one telephone reminder to complete follow-up assessments.

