While psychological interventions have an arguably prominent role in managing all three of these unmet needs, few resources have been developed for this population, particularly resources that utilise self-care and support self-management. Indeed, our 2018 systematic review of interventions for MBC identified only 15 RCTs that have been conducted to date [12]: Overall, interventions improved distress, coping, and pain. For quality of life, sleep, and fatigue, the evidence was insufficient to form recommendations [12]. Since 2018, four additional RCTs have been published (two group-based, one individual-based, one low intensity) [13–16]. Three were pilot trials which found evidence of feasibility [13–15], while the fully powered RCT of a 12-month weekly group program found evidence of improved depression, anxiety, and QOL compared to a no-treatment control [16]. Overall, group therapy has the strongest evidence base with nine published trials [12, 16], but had the correspondingly poorest uptake/adherence [12]. The intensity of these services/interventions precludes participation by women with high symptom burden, who live in rural/remote areas, are living with socioeconomic disadvantage, or have occupational or carer demands. Personal barriers to seeking psychological interventions also exist, including perceived stigma [17], and fear of being distressed by others’ decline or death [18]. There are also significant workforce barriers, where the demand for existing psychological services exceeds supply [19]. In contrast, while low-intensity interventions (to date) have the weakest evidence base (five trials published: three telephone-based, two expressive writing, nil online), they have the highest uptake and adherence [12, 14]. In sum, given women with MBC face intensive medical treatment schedules, are frequently unable to commit to future appointments, and may have compromised health status [11, 12], future research needs to design and trial interventions that can yield efficacy while minimising participation burden.

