Digital health tools, such as web-based therapy, could address these barriers. Given digital health tools provide 24/7 access at a time and place convenient to the patient, and reduce obligations to spend valued time and money in healthcare settings, this mode of providing psychosocial care has particular pertinence to women with MBC [20]. Furthermore, digital interventions are easily scalable, can be immediately updated as new evidence emerges, and provide the flexibility to explore content in a non-linear way, with patients able to access information pertinent to their most immediate needs [21]. While there are no published online intervention RCTs in this population, women with MBC are already seeking cancer-related information on the internet [20] and are receptive to the online provision of a psychosocial program [22]. The rapidly building evidence base in *early-stage* cancer populations for improving distress [23, 24], depression and anxiety [25], fear of recurrence [26], QOL [27, 28], and health service utilisation [27], can help to inform future MBC-specific intervention development.

Our team recently developed and usability-tested an online program to support women with MBC: *Finding My Way-Advanced (FMW-A)* [29]. FMW-A was co-designed, with content initially sourced and adapted from our evidence-based *Finding My Way* web-program for people with *early-stage* cancer [27, 28]. The content was authored by a senior clinical psychologist with expertise in psycho-oncology (LB), with iterative rounds of input and feedback from a multidisciplinary co-design team including consumers, clinicians, and academics. A qualitative think-aloud protocol was then implemented to test usability of the resulting 6-module prototype, with women living with MBC accessing up to three modules with an interviewer sitting alongside. Feedback summarised the supportive and informative nature of the program, supplemented by comments about broadly relatable content. However, within themes, diverging experiences emerged regarding navigability, worksheets and layout. Participants noted that having/making time for the intervention would be important to program engagement [29]. Pragmatic issues were corrected prior to feasibility pilot testing, which demonstrated feasibility via an uptake rate of 61%, a retention rate of 66%, and an engagement level of 2.3 modules [30], which was in line with prior online intervention research, and sufficient to impact outcomes [27].

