### Measures

Table 2 outlines the efficacy outcomes that will be assessed using a battery of validated self-report measures at baseline, post-intervention (primary endpoint), 3-month and 6-month follow-ups, supplemented with website usage data and patient health service use data obtained via data linkage of government databases (‘Services Australia’). Figure 3 outlines the schedule of assessments.

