#### Primary outcome: mental QOL

Mental QOL will be measured using the EORTC QLQ C-30 emotional functioning subscale [33]. Total scores range from 0 to 100, with higher scores indicating better functioning. QOL has been selected as the primary outcome as it is one of two priority outcomes for MBC nominated by Cancer Australia [2], and has not had sufficient focus in earlier trials [34]. Furthermore, it is a meaningful outcome to patients [2], correlates well with other clinical outcomes and is demonstrated to be sensitive to change [35, 36].

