#### User satisfaction

User satisfaction will be assessed using single Likert-style items in the follow-up questionnaire asking participants how helpful they found aspects of the program, and how confident they felt they could apply the program to their everyday life, and through qualitative interviews.

**Table 2 Tab2:** Measures of Secondary Outcomes, Sample Characteristics, and Baseline Covariates

Domain/Measure	Description
Secondary Outcomes	
QOL	Other dimensions of quality of life will be measured by the EORTC QLQ-C30 subscales (global QOL; physical, social, role, cognitive functioning; physical symptoms) [33].
Distress	The 21-item Depression Anxiety Stress Scale [37]. Assesses anxiety, depression and stress over the previous week; total distress score will be used. The total scale score of the 17-item Post-traumatic Stress Scale-Self-Report (PSS-SR) will be used to measure cancer-specific distress [38]. Items measure symptoms experienced over the past week, rated on a 4-point scale (0 = not at all to 4 = almost always), and anchored to cancer diagnosis as the stressor. Higher scores indicate higher cancer-specific distress
Fear of Progression	The English-version of the 12-item Fear of Progression Questionnaire short form measures levels of anxiety regarding cancer progressing on a five-point Likert scale from 1 (‘never’) to 5 (‘very often’) [39].
Unmet needs	34-item Supportive Care Needs Survey – Short Form [40]. Measures perceived psychosocial, information, physical/activity of daily living, patient care and sexuality needs.
Cost utility	The EuroQol 5 dimensions 5 level (EQ-5D-5L) is a generic preference-based measure [41]. Based on Australian-specific algorithms ranging from − 0.281 to 1, utility scores will be converted into quality adjusted life years (QALYs) required for cost-utility analysis.
Participant Characteristics and Covariates (collected at baseline only)	
Socio-demographic characteristics	Age, marital status, sexual orientation, children, occupational status, annual gross income, educational attainment level, area of residence/postcode, ethnicity.

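### The reminder procedure describes no short route to the primary outcome; offering a 35-item form at the last two reminders is a cheap way to recover some of it

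*Protocol article*

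**What the plan says.** Under Study procedures and timeline, the article sets out how follow-up non-response is handled: "Non-responders will receive two automated email reminders, and one telephone reminder to complete follow-up assessments". Nothing is said there about a reduced questionnaire.

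The Measures section describes the content as a "battery of validated self-report measures at baseline, post-intervention (primary endpoint), 3-month and 6-month follow-ups". Table 2 lists the instruments. They include "The 21-item Depression Anxiety Stress Scale", a 17-item PSS-SR, a 12-item Fear of Progression short form and the "34-item Supportive Care Needs Survey". For the QLQ-C30, Table 2 says: "Other dimensions of quality of life will be measured by the EORTC QLQ-C30 subscales". The Health economics section adds the EQ-5D-5L at every assessment. Social support and the sociodemographic and medical items are collected at baseline only.

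The primary outcome is much smaller than this battery: "Mental QOL will be measured using the EORTC QLQ C-30 emotional functioning subscale".

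On retention, the Background reports from the pilot "an uptake rate of 61%, a retention rate of 66%, and an engagement level of 2.3 modules". The sample size section allows for 20% attrition, the top of the 4-20% range it cites for low-intensity interventions in this population, and also refers to pilot data.

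**The concern.** As the procedure reads, a woman who has not answered is asked up to three more times for the same long assessment, although the trial most needs one subscale of it. The Background describes this population as living with pain, fatigue and insomnia. It is plausible that some women who would not start about 119 items would answer about 35.

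Two things are at stake. Each missing primary score costs power, and the pilot's loss was larger than the loss planned for. The mixed model also relies on data being missing at random, and women too unwell or distressed to complete a long survey are a plausible exception when the outcome is emotional functioning.

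**Working it through.** **Items per follow-up.** QLQ-C30 30 (taken from the instrument's name; the article gives no count), DASS 21, PSS-SR 17, Fear of Progression 12, Supportive Care Needs 34, EQ-5D-5L 5 (taken as its five dimensions).

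30 + 21 + 17 + 12 + 34 + 5 = 119, before the satisfaction items.

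QLQ-C30 plus EQ-5D-5L: 30 + 5 = 35. The scales that would become optional: 21 + 17 + 12 + 34 = 84.

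**Reproducing the plan's sample size.** Inputs from Sample size and justification: difference 4, SD 20, rho 0.6, one baseline and three post-baseline measures, 80% power. Alpha is not stated; two-sided 0.05 is assumed.

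- Repeated-measures ANCOVA variance factor: (1 + (r − 1)·rho)/r − rho². With r = 3: (1 + 1.2)/3 − 0.36 = 0.3733.
- Effective variance: 400 × 0.3733 = 149.33.
- Required n for 80% power: 147 per arm, as stated. One-sided 0.05 would give 116, which supports the two-sided assumption.
- With 20% attrition: 147/0.80 = 183.75, so 184 against the stated 185. This agrees closely.

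**Power under different recovery rates.** Let R be retention and q the share of non-responders recovered. Analysable n per arm = 185 × [R + (1 − R)·q], and power = Φ(4/√(2 × 149.33/n) − 1.96). The documents give no value for q, so a range is shown.

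| Retention before fallback | q | n per arm | Power |
|---|---|---|---|
| 80% (planned) | 0 | 148.0 | 80.4% |
| 80% | 10% | 151.7 | 81.3% |
| 80% | 25% | 157.3 | 82.7% |
| 80% | 50% | 166.5 | 84.8% |
| 66% (pilot) | 0 | 122.1 | 72.5% |
| 66% | 10% | 128.4 | 74.6% |
| 66% | 25% | 137.8 | 77.6% |
| 66% | 50% | 153.6 | 81.8% |

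**Recovery needed at pilot loss to return to 147 per arm.** (147/185 − 0.66)/0.34 = (0.7946 − 0.66)/0.34 = 0.396, so about 40% of non-responders.

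**What these figures do not cover.** They use the plan's average over three visits and treat a non-responder as missing all three. The mixed model will use any visit that is available. They are also not the power of the post-intervention contrast. With one follow-up the variance factor is 1 − 0.36 = 0.64; the same inputs then need 252 per arm, and 148 per arm gives 57.6%.

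**The case against.** The strongest reply is that nothing here is wrong or contradictory. Two emails and a call form a normal schedule. Survey order, saving of partial answers and the wording of reminders are operational details that a journal article may leave to the full protocol, and Figures 2 and 3 are not shown. If the QLQ-C30 already comes first and partial answers are kept, women who start and then stop already supply the primary score. That stands. The remaining gap is women who never open the survey.

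A reader might infer that primary data are being lost because of questionnaire length and that a short form would get them back. The documents do not support that. No section attributes non-response to length, and the article does not say how the pilot measured retention or why women were lost. Entry requires an estimated life expectancy above 6 months, while the last assessment falls about 7.5 months after enrolment (6 weeks plus 6 months). Death, deterioration and withdrawal are therefore plausible causes of loss, and no form recovers them.

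A reader might also cite the Background's call for future research to "trial interventions that can yield efficacy while minimising participation burden" as a standard the plan breaks. That sentence concerns the burden of interventions, not of questionnaires.

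Finally, the change shifts missingness onto distress, fear of progression and unmet needs, all named in the secondary hypotheses. That cost is real and has not been quantified. Confining the offer to the last two reminders limits it.

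**Conclusion.** The point holds as a low-cost improvement to a stated procedure. The described follow-up of non-responders has no short route to the primary outcome, each follow-up carries about 119 items, and pilot retention was 66% against 80% planned.

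The benefit is uncertain and partial. The gain is about 1 to 4 percentage points of power at the planned loss (80.4% to 81.3-84.8%) and about 2 to 9 at the pilot's loss (72.5% to 74.6-81.8%). This rests on an assumed recovery of 10 to 50%, two-sided 0.05, and the plan's three-visit averaging. Getting back to 147 per arm from the pilot's loss would need about 40% recovery, which should not be counted on. The missing-at-random assumption would still be needed for those who remain missing.

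The difference between pilot retention and the attrition allowance is a sample-size question in its own right. A short form would ease it but does not settle it.

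**What to change.** At the second email and the telephone reminder, in both arms alike, offer a stand-alone online form containing the whole QLQ-C30 and the EQ-5D-5L, with the remaining scales optional. Give priority to the post-intervention assessment, the primary endpoint. Keeping the QLQ-C30 whole preserves the other QOL domains as well as the primary subscale; with the EQ-5D-5L, it also keeps the effect measures for both health-economic outcomes. Record which form each woman completed.

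If not already done, put the QLQ-C30 first in the full survey and keep partial responses.

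The cost is a second Qualtrics link, revised reminder wording and a minor ethics amendment. No contacts are added to those already planned. The downside is that some late responders who would have completed everything will choose the short form, losing their distress, fear-of-progression and unmet-needs scores at that visit.

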**Fig. 2 Fig2:**
[figure not shown]
Flow chart of participants through the FMW-A study

### Qualitative examination of user satisfaction

A subset of participants from intervention and control groups will be contacted by telephone at 10-weeks post baseline to schedule a telephone interview for the purposes of obtaining qualitative feedback on user satisfaction with the intervention and/or resources offered as the control condition. Approximately 20 participants will be approached in order of enrolment until saturation of themes occurs. Consenting participants will then be sent a topic guide via email 2 weeks prior to their scheduled interview. Telephone interviews will be conducted and audio recorded, and participants can review their transcripts if requested.

